#### Perinatal factors with relevance for maternal concern and mother-child attachment

The following elements will be reviewed:

- Planned pregnancy
- Infertility
- Previous pregnancies
- Due date
- Time for quickening
- Known fetal gender before birth
- Numbers of ultrasounds in this pregnancy

### Demographic information

Maternal age, weight, height, educational level, marital status, smoking habits and country of origin will be obtained from copy of the standard form for antenatal care (“Helsekort for gravide”).

### Information about fetal movements

This enables us to evaluate maternal experiences with the information about fetal movements and the subjective user-friendliness and utility value of the information. No measurement scales exist, and questions are made for this study. A four-point Likert scale ranging from 1 (do not agree at all) to 4 (completely agree) will be used.

### Experiences with FMC

No measurement scales exist to evaluate the users’ satisfaction with FMC. Questions were made for this study, including perceived stress, irritation, tiredness with practicing FMC, feeling guilty if not practicing FMC, and if FMC intrudes in other activities for the mother or in other ways affect her quality of life. A four-point Likert scale ranging from 1 (do not agree at all) to 4 (completely agree) will be used.

### Experiences if examined because of DFM

Maternal evaluation of quality of the encounter with a midwife or a doctor if examined because of concern will give important information on the women’s experiences of being given power from health professionals in her assessments of fetal activity. Questions were made for this study. Patient’s perceptions of quality of care are considered in two dimensions; medical-technical competence of the caregivers and the attitudes and actions of the caregivers. A four-point Likert scale ranging from 1 (do not agree at all) to 4 (completely agree) will be used.

## Data analyses

Data handling will be performed in SPSS 14.0. Best suited statistical methods will be chosen in the analyses. Participants will be handled according to the intention-to-treat-principle.

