# Aim and outcome measures

The aim is to test effects of using formal kick counting chart in the third trimester of pregnancy in an unselected population. The research questions are:

Does Fetal Movement Counting:

1. Improve the identification of risk pregnancies / pathology?

*Primary outcome measures*: Numbers of identified pathological conditions in pregnancies (fetal growth restriction (FGR), acute caesarean section on fetal indication/non–reactive non-stress test (NST), oligohydramnios, pathologic blood flow in arteria umbilicalis, maternal perception of absent fetal movements for more than 24 hours before admission to hospital, or perinatal death).

*Secondary outcome measures*: Frequency of consultations because of maternal concern, use of resources in evaluation of these pregnancies (NST, ultrasound, Doppler, recurrent consultations), induced or spontaneous start of delivery, mode of birth.

1. Affect the women’s well-being?

*Primary outcome measure*: Maternal concern.

*Secondary outcome measure:* Maternal satisfaction with use of FMC and sense of control in interpretation of signals from own body and child.

1. Stimulate maternal-fetal attachment antepartum?

*Primary outcome measure*: Maternal-fetal attachment.

*Secondary outcome measure:* Health promoting behavior in pregnancy (smoking habits, use of alcohol, attending standard program for antenatal care).

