## Recruitment of responders and data collection

Women will be recruited from the hospitals’ lists over women having been at the ultrasound screening in pregnancy week 17-19. A flow chart over data collection is appended (Appendix 1). All women will receive a letter in pregnancy week 23-24, asking to participate in a study of attitudes during pregnancy with a random possibility to be asked to perform FMC in the third trimester. Mothers, who agree to participate, do this by signing an informed consent and completing a baseline questionnaire (QI). On completion of the baseline inventories, but before inspection of the results, an assistant will perform the randomization into the FMC-group and the control group.

Women in the FMC-group will be asked to count fetal movements daily from gestational week 28. These women will be telephoned one week after commencement, to discuss questions or problems with the charting technique. Women in the control group will be told about the next survey at 34 weeks of gestation. Women in both groups will be asked to perform prospective, structured registrations – like a diary - if they were concerned about DFM and return these diaries to the study group after the delivery.

The questionnaires will be distributed in pregnancy weeks 24 (questionnaire I) and 34 (II). Answering the questionnaires can be done either by paper or by web-pages with interactive questions. An appropriate web-solution will be used for electronic data collection. Alternative retrieval for paper version: Scanning of questionnaires at the NIPH.

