#### Maternal well-being

The Cambridge Worry Scale (CWS)59 has demonstrated good reliability and validity60, also in a Scandinavian population61. The measure contains 16 items, measuring women’s major worries during pregnancy in a four-factor structure; socio-medical, own health, socio-economic and relational aspects. Responses are made on a 6-point Likert-type scale (from 0=”not a worry” to 5=“extremely worried”). An open-ended question at the end allows the respondents to tell about other worries not in the list.

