## Overview over data collection

|  | Survey I | Survey II | Copy of case notes |
| --- | --- | --- | --- |
| Maternal-fetal attachment |  | x |  |
| Mental well-being | x | x |  |
| Maternal depression level | x |  |  |
| Self-efficacy | x |  |  |
| Self-esteem | x |  |  |
| Experiences with FMC to the intervention group |  | x |  |
| Experiences if examined because of DFM |  | x |  |
| Demographic details | x |  | x |
| Obstetric history |  |  | x |
| Planned pregnancy | x |  |  |
| Number of US’s in this pregnancy |  | x |  |
| Known fetal gender | x | x |  |

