## Maternal concern

The goal is to identify no increase in the level of concern in the intervention group. In the original study with 1207 respondents in the 16 items (0-5) inventory with a 6-point Likert scale, unweighted mean scores across items and standard deviations for the survey in pregnancy week 35 were 1.13 (0.65)59. Detectable changes are estimated to be a change in mean of 0.12, which give an estimated sample of 462 participants in each arm of the trial with 80% power and a significance level of 0.05.

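### Maternal concern: the Survey I worry score is left out of a comparison sized on late-pregnancy means alone, and the deciding contrast is left to the analysis stage

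*Protocol*

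**What the plan says.** The section Aim and outcome measures makes maternal concern the primary outcome for the question on women's well-being. The instrument, described under Maternal well-being, is the Cambridge Worry Scale: "The measure contains 16 items, measuring women’s major worries during pregnancy in a four-factor structure". The overview of data collection has the row "Mental well-being | x | x", which marks Survey I and Survey II. No row is headed maternal concern; reading this one as the worry scale follows from the other two sections.

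Under Recruitment of responders and data collection, the surveys go out in weeks 24 and 34. Women enter by consenting and completing the first questionnaire, and are randomised only after that. The first worry score is thus a true baseline, available for essentially every randomised woman.

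Section 8.2 (Maternal concern) states: "The goal is to identify no increase in the level of concern in the intervention group". It takes a mean of 1.13 and SD of 0.65 from a published week-35 survey, then says "Detectable changes are estimated to be a change in mean of 0.12", giving 462 per arm at 80% power and a 0.05 level. The Sample section plans 538 per arm.

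On method, Data analyses offers intention to treat and the sentence "Best suited statistical methods will be chosen in the analyses".

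**The concern.** A continuous outcome with one baseline and one follow-up has three standard between-arm contrasts: the week-34 score alone, the change from baseline, and the week-34 score adjusted for baseline. In a randomised trial all three estimate the same effect, but their standard errors differ and so do their p-values in the same data.

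Two things are at stake. First, precision: the sample size makes no use of a baseline that the trial already collects. Second, credibility: the protocol places the choice of method at the analysis stage for a primary outcome, so a borderline result could depend on which contrast is reported. Because the stated goal is to see no increase in concern, that freedom matters in both directions. A significant contrast could be picked out, or a non-significant one could be reported and a real increase missed.

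**Working it through.** **Inputs.** From section 8.2: difference 0.12, SD 0.65, level 0.05, power 80%, 462 per arm. From Sample: 538 per arm. Assumed, because the protocol does not give it: baseline to week-34 correlation r of 0.3, 0.5 or 0.7. The change score also needs an assumed equal SD at both surveys.

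**The plan's own figure.** n per arm = 2 × (1.96 + 0.8416)² × 0.65² / 0.12² = 460.6, so 461 against the stated 462. It reproduces as a two-sided, unadjusted comparison of follow-up means. A one-sided 0.05 test gives 363 and does not reproduce. Treating 0.12 as a non-inferiority margin at one-sided 0.025 also gives 461, so the figure does not separate those two readings; the gain in precision applies to both.

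**Effective SD of each contrast.**
- Week-34 score: 0.65.
- Change score: 0.65 × √(2(1 − r)) = 0.769, 0.650, 0.503 for r = 0.3, 0.5, 0.7.
- Baseline-adjusted (ANCOVA): 0.65 × √(1 − r²) = 0.620, 0.563, 0.464.

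**Power for 0.12**, as Φ(0.12 / (SD × √(2/n)) − 1.96). Example, week-34 score at n = 462: 0.65 × √(2/462) = 0.0428; 0.12 / 0.0428 = 2.81; Φ(0.85) = 80%.

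| Contrast | n per arm | r = 0.3 | r = 0.5 | r = 0.7 |
|---|---|---|---|---|
| Week-34 score | 462 | 80.1% | 80.1% | 80.1% |
| Change score | 462 | 66.0% | 80.1% | 95.2% |
| Adjusted | 462 | 83.7% | 90.0% | 97.6% |
| Week-34 score | 538 | 85.7% | 85.7% | 85.7% |
| Change score | 538 | 72.5% | 85.7% | 97.4% |
| Adjusted | 538 | 88.8% | 93.8% | 98.9% |

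**Sample needed for 80% power.** Adjusted: 460.6 × (1 − r²) = 420, 346, 235 per arm. Change score: 460.6 × 2(1 − r) = 645, 461, 277. The adjusted analysis never needs more than the 462 already stated. The change score needs more than 538 when r is below 1 − 538 / (2 × 460.6) = 0.42.

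**Free choice, no true effect.** With 4 million null draws per correlation, at least one of the three contrasts was significant at 0.05 in 9.2%, 9.7% and 10.1% (r = 0.3, 0.5, 0.7). A check with 20,000 simulated trials of 462 per arm gave 9.1%, 10.1% and 10.0%, with each single test near 5%.

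**Free choice, true increase of 0.12, 462 per arm.** All three contrasts were significant in 59.7%, 68.9% and 77.6%. At least one was therefore non-significant in 40%, 31% and 22%, against 20% for the week-34 score alone.

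**The case against.** The strongest reply is that the choice of model belongs in a statistical analysis plan, which is not at hand. Most of that stands: a protocol that simply left the model unmentioned would be no finding. Here, however, the protocol says something: methods are chosen in the analyses. It points to no later plan, and its time schedule starts data analyses in January 08, after recruitment is due to end. That wording is worth correcting whatever a later plan contains.

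Four stronger readings are tempting, and the protocol does not support them.

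- *That section 8.2 means change from baseline, or is evenly split between contrasts.* Section 8 uses change for the effect of the intervention. Section 8.3 does the same for attachment, which the overview table collects only in Survey II. With a single-survey SD and a figure that reproduces for follow-up means, section 8.2 most naturally sizes an unadjusted between-arm difference in late pregnancy.
- *That the false-positive rate is doubled.* The 9–10% arises only if all three contrasts are examined and any significant one is reported. The protocol does not say the choice follows the results; if one contrast is fixed beforehand, the rate is 5%. Half of such false positives would also be apparent decreases, which are not what the goal is about.
- *That the trial is underpowered.* The 66% for a change score is at 462 per arm. At the planned 538 it is about 73%, and only if r is as low as 0.3.
- *That an unadjusted analysis is wrong.* It is valid in a randomised trial and has its 80% power at 462. Adjustment is an improvement, not the repair of an error.

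**Conclusion.** The point holds as an improvement available at no cost, together with a wording problem that should be closed. The protocol sizes maternal concern on late-pregnancy means, gives the baseline score no role, and leaves the deciding contrast to the analysis stage. Baseline adjustment would take power from 80% to 84–98% at 462 per arm, and from 86% to 89–99% at 538.

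These ranges rest on an assumed correlation of 0.3 to 0.7 and on the cited SD of 0.65 applying at week 34. They also take every randomised woman as analysed, since the protocol states no allowance for dropout. The direction does not depend on the assumed value: adjustment is at least as precise as either alternative in a trial of this size. The false-positive rate of about 9–10%, and the 22–40% chance that some contrast misses a true increase of 0.12, are upper bounds on what free choice could do, not predictions of what the investigators will do.

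**What to change.** In Data analyses, state in advance that the primary contrast for maternal concern is the between-arm difference in mean week-34 Cambridge Worry Scale score (unweighted mean over the 16 items), estimated by linear regression (ANCOVA) adjusted for the Survey I score. Name the change from baseline as supportive only.

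In section 8.2, reword the 0.12 as a between-arm difference at week 34, and keep 462 per arm as a conservative figure for the adjusted analysis. If a separate analysis plan already fixes the contrast, refer to it in place of the present sentence on method.

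The cost is one or two sentences. No new data, questionnaires or participants are needed, because Survey I already carries the baseline score.

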## Overview over data collection

|  | Survey I | Survey II | Copy of case notes |
| --- | --- | --- | --- |
| Maternal-fetal attachment |  | x |  |
| Mental well-being | x | x |  |
| Maternal depression level | x |  |  |
| Self-efficacy | x |  |  |
| Self-esteem | x |  |  |
| Experiences with FMC to the intervention group |  | x |  |
| Experiences if examined because of DFM |  | x |  |
| Demographic details | x |  | x |
| Obstetric history |  |  | x |
| Planned pregnancy | x |  |  |
| Number of US’s in this pregnancy |  | x |  |
| Known fetal gender | x | x |  |

# Time schedule

| **Data-collection/focus** | **Started/estimated started** | **Estimated to be finished** |
| --- | --- | --- |
| Preparation of the studies | Sept 06 | April 07 |
| RCT: information versus fetal movement counting | Recruiting respondents: May 07 | December 07 |
| Data analyses: January 08 | January 09 |
| Publication of four scientific articles |  |  |
| 1) Maternal perception of fetal movements in a total population – two cross-sectional surveys |  | June 07 |
| 2) FMC and identification of perinatal risk factors |  | March 08 |
| 3) FMC and maternal concern |  | October 08 |
| 4) FMC and maternal-fetal attachment |  | January 09 |

# Ethics and applications

The Femina-study and “Tell Trivselen” are approved by the Regional Committee for Medical Research Ethics. Femina is advised by The Norwegian Data Inspectorate and “Tell Trivselen” was advised by The Norwegian Data Inspectorate in June 2006. The study will be applied for accept by the Regional Committee for Medical Research Ethics, The Norwegian Data Inspectorate and Sosial- og Helsedirektoratet, and will be reported to the database for clinical trials ([www.clinicaltrials.gov](http://www.clinicaltrials.gov/) ) before start.

All participants will be invited to contact the study group by telephone or by mail. This will ensure that anxious and worried women could get advices about how to get appropriate help if needed. According to this, participants in the intervention group will be contacted by telephone one week after FMC start. This is to increase the compliance to the counting and to ensure correct interpretation of the instructions about the counting method.

# Budget for the RCT

| PhD scholarship (75% time) | NOK 1.456.000 |
| --- | --- |
| Operating expenses | NOK 100.000 |
| Payment for recruiting midwifes | NOK 648.000 |
| Printing of questionnaires | NOK 120.000 |
| IT consultant for interactive questionnaires | NOK 40.000 |
| Total | NOK 2.364.000 |

# Power analyses

Estimations of sample size needed to preserve the needed power vary widely with the issue being studied. Some examples on how effects of sample size will affect some of the measurements in this study are done by evaluating the effect of the intervention. This is done with the computer program PS Power and Sample Sizes62. The effects of changes is estimated by relative risk for dichotomous variables and means with standard deviations for continuous variables Power analyses only for the three primary outcomes are included here.

## Identification of risk pregnancies

The goal is to increase the accuracy of maternal perception of DFM as a predictor for need of examination or intervention. This will be measured by a compound measure of rates of identification of risk pregnancies related to DFM. Prevalence of risk conditions are estimated from preliminary results of Femina (unpublished) or the Norwegian Birth Register.

| Condition | Prevalence |
| --- | --- |
| Fetal distress: Acute caesarean section on fetal indication (excl protracted birth), non-reactive NST, pathological levels of fetal scap-pH or Apgar5 min ≤ 3 | 8 % |
| Fetal growth restriction < 2.5 centile or pathological Doppler flow in arteria umbilicalis | 5 % |
| Absent fetal movements for more than 24 hours | 0.5 % |
| Intrauterine death | 0.02 % |
| Estimated prevalence of compound measure | 13.52 % |

The goal is a 10% increase of identification of these risk pregnancies, which gives an estimated sample of 538 in each arm of the trial with 80% power and a significance level of 0.05.

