# The Femina collaboration and projects

The Fetal Movement Intervention Assessment (Femina) collaboration engages several researchers worldwide with different aims and approaches.

Fetal activity serves as an indirect measure of central nervous system integrity and function, and regular FM can be regarded as an expression of fetal well-being1;2. Pregnancies in which the mother report decreased fetal movements (DFM) may indicate danger for the fetus2;3, and is associated with adverse outcomes as fetal hypoxia, growth restriction, preterm birth and stillbirth4-7. The unborn child responds automatically to hypoxia by redistributing blood flow away from the non-essential organs8 and reduction of non-vital activities9; *movements*. DFM is experienced by 4-15% of all pregnancies3;4.

Femina started in May 2004, with registration of the women seeking to 14 Norwegian hospitals for their worry because of DFM. Another 14 hospitals are participating in the UK, USA, Australia and New Zealand. The overall aim is to improve pregnancy health, pregnancy outcomes and child health through better understanding, awareness and management of fetal activity in general and DFM in particular. This include improving knowledge and clinical management through 1) Learning their epidemiology and outcome, 2) Improving the quality of care by health professionals, 3) Improving maternal information and vigilance, 4) Exploring the basic associations between fetal activity and outcome, 5) Testing new and improved approaches to fetal movement counting and 6) studying fetal growth and placental pathology in pregnancies with DFM.

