The literature describes inconsistent and overmedicalized policies regarding the identification, assessment and monitoring of DFM3;10;11. There is a lack of evidence based knowledge of “normal” vs. “abnormal” fetal movements. Apparent “limits of normality” are mostly based on high risk pregnancies and concepts of DFM4;12. Femina has documented a wide spread of the health professionals’ view on FM’s relevance and significance as a marker for fetal well-being11, and there are large variations in management when women present their concern because of decreased fetal movements, how, and to what extent these risk pregnancies are identified in the population3. None of the hospitals involved in Femina in Norway had written guidelines before Femina started. They have however, responded to this sub-standard situation by consensus-driven quality-improvement projects starting in November 2005 on the two issues that need to follow each other – information to women and in-hospital management.

Femina has prospectively collected a population-based cohort of more than 5500 cases from about 82 000 pregnancies. Preliminary results from Femina have shown significant possibilities for clinical quality improvements with regard to *management* in pregnancies with DFM and *maternal perception* to fetal movements. Our results show that most mothers in our population did interpret their baby’s FM as a sign of good health, but that what they considered a reason for concern varied greatly – ranging from concerns because their baby kicked less than their friends baby (17%), to not contacting health professional even with total absence of FM (unpublished), and the few that actually contacted health professionals frequently receive non-productive or even dangerous information, ranging from telling the mother that she should feel 25 kicks/hour, to “reassurance” that it is only DFM after total absence of FM for over 24 hours11. In our Norwegian population, 50% waited more than 24 hours without any FM before they contacted health professionals. They did not understand the urgency and severity of this sign. When finally contacting help, they received variable help, as management consumed considerable health resources without any guidelines or monitoring of outcomes3;11. With lacking information to health professionals and pregnant women, as much as 50% of women affected by stillbirth perceive a reduction of FM, in many cases for several days before death4;5;13-15.

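### The 13.52% planning rate in section 8.1 is a sum of condition prevalences, while the compound measure it stands for is defined there as identification related to decreased fetal movements

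*Protocol*

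**What the plan says.** Protocol section 8.1 (Identification of risk pregnancies) describes the first primary outcome as a "compound measure of rates of identification of risk pregnancies related to DFM". It then gives the source of the planning rate: "Prevalence of risk conditions are estimated from preliminary results of Femina (unpublished) or the Norwegian Birth Register". Four rows follow: fetal distress at 8%, growth restriction or abnormal umbilical Doppler at 5%, absent movements for more than a day at 0.5%, and intrauterine death at 0.02%. The bottom line is "Estimated prevalence of compound measure | 13.52" per cent. From this rate and a 10% increase the section derives 538 per arm, and the Sample section adopts that number for the trial.

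The outcome is described in two other places, and they do not agree. The Methods section on identification of perinatal risk factors ties the primary outcome to consultations prompted by what the mother perceives as reduced movement. Its own list, however, includes growth restriction found only at birth and perinatal death. The section on aims and outcome measures lists pathological conditions with no DFM restriction.

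The opening section on the Femina collaboration gives two figures for how common DFM is. The registry, which records women who come to hospital because of it, holds "more than 5500 cases from about 82 000 pregnancies". As general background, "DFM is experienced by 4-15% of all pregnancies".

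**The concern.** A planning rate has to be the control-arm rate of the endpoint that will be counted. How often a condition occurs in all pregnancies is a different quantity from how often it is picked up because the mother noticed reduced movement. The second requires a DFM presentation, so it cannot exceed the share of women who present. Section 8.1 defines the second quantity and tabulates the first.

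The total also adds the four rows as if no pregnancy could fall in two of them, although growth restriction or abnormal Doppler and fetal distress may well occur in the same pregnancy.

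What is at stake is the effect that 538 per arm can detect. For a given number per arm, a lower base rate means that a larger relative effect is needed for the same power.

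**Working it through.** **Inputs.** From section 8.1: 8%, 5%, 0.5% and 0.02%; total 13.52%; 538 per arm; 80% power; significance level 0.05 (taken as two-sided; the protocol does not say). From the Femina section: 5500 cases, 82 000 pregnancies, and a 4-15% range for women who experience DFM.

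**The plan's own figures.**
- Total: 8 + 5 + 0.5 + 0.02 = 13.52. It reproduces exactly, as a plain sum.
- 538 per arm does not reproduce. With the usual pooled-variance formula, a relative 10% increase (13.52% to 14.87%) needs 10 460 per arm and an absolute one (13.52% to 23.52%) needs 236. One-sided, continuity-corrected, unpooled and arcsine variants do not give 538 either. That is a separate fault. Here it means that the detectable effects below have to be solved from n = 538.

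**DFM-related reading.**
- Presentation share in Femina: 5500/82 000 = 6.71%.
- Ratio: 13.52/6.71 = 2.02.
- At the top of the background range: 13.52/15 = 0.90, so about 90% of women experiencing DFM would need a listed condition. At any share below 13.52% the rate is unattainable.

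**What 538 per arm detects.** With p0 the control rate, p1 the intervention rate and p̄ their mean:

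n = [1.96·√(2p̄(1−p̄)) + 0.8416·√(p0(1−p0) + p1(1−p1))]² / (p1−p0)²

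Solving for p1 at n = 538:

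| Base rate p0 | Detectable p1 | Difference | Risk ratio |
|---|---|---|---|
| 13.52% | 19.9% | 6.4 points | 1.47 |
| 6.7% | 11.6% | 4.9 points | 1.73 |

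Check of the second line with p0 = 0.0671 and p1 = 0.1163: p̄ = 0.0917; first term 1.96 × 0.4081 = 0.800; second term 0.8416 × 0.4067 = 0.342; (1.142)²/0.0492² ≈ 539, which agrees up to rounding of p1.

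The 6.7% line treats every presentation as showing a listed condition, so it is the favourable limit for a population like Femina's.

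**Any-route reading.** The share of women with at least one of the four rows is:
- 13.52% if no pregnancy has two conditions;
- 1 − (0.92 × 0.95 × 0.995 × 0.9998) = 13.05% if the rows are independent;
- 8% if all other cases fall inside the fetal-distress row, which is the extreme.

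At 13.05%, power for a risk ratio of 1.47 with 538 per arm is about 78% instead of 80%.

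**The case against.** The strongest reply is that the DFM wording is loose and the endpoint is any-route. The aims section carries no DFM restriction, and two items in the Methods list need no DFM presentation. On that reading prevalence is close to the right base, there is no 6.7% ceiling, and the overlap correction is small on the figures given. This stands, and it limits the point to two definitions that need reconciling. It does not remove the point, because section 8.1 and the Methods text both state the DFM link.

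The protocol also calls 538 preliminary, to be reassessed during inclusion, and presents its power calculations as examples. That makes correction easier, but a reassessment still needs a rate that matches the endpoint.

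A reader might infer more than the document supports:
- *That the control arm cannot reach 13.52%.* This holds only for DFM-related identification in a Femina-like population. Both cohort counts are approximate, and the trial recruits from hospitals outside Femina.
- *That counting cannot change the tabulated rates.* It can. Non-stress tests and Doppler findings exist only if the test is done, acute caesarean is a care decision, and time without movement before admission depends on when the woman comes. The protocol itself expects that counting might lead to more intervention.
- *That overlap roughly halves the power.* At 8%, power for a risk ratio of 1.47 would be about 54%, but nothing in the protocol supports full nesting, and 1.47 is solved from 538 and stated nowhere.
- *That the detectable risk ratio is far above 1.73.* This needs an assumed share of presentations with pathology, for which the document gives no figure.

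Finally, the harm from a lower base depends on the effect scale. If the 10% were absolute, power at 538 would be about 99% at 13.52% and would not fall at a lower base. The Power analyses section, however, says that dichotomous outcomes are handled as relative risks.

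**Conclusion.** The point holds as a mismatch between the planning rate and the endpoint definition, made worse by outcome definitions that disagree across three sections.

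On the DFM-related reading, 13.52% is implausible: twice the presentation share in the sponsor's own cohort, and attainable at the 15% upper figure only if about nine in ten women experiencing DFM have a listed condition. The detectable risk ratio with 538 per arm rises from 1.47 to 1.73 at a base of 6.7%. This assumes a two-sided 0.05 test, 80% power, equal arms, and trial hospitals that resemble Femina's.

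On the any-route reading, the error is only that the sum is an upper bound for the tabulated rows, and the likely effect is modest (13.05% under independence). The protocol does not say which row comes from which source or whether cases were already counted once, so the true overlap is unknown.

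Correcting the rate will not by itself repair the sample size, since 538 does not follow from 13.52% and a 10% increase on either scale.

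**What to change.** 1. Choose one definition of the first primary outcome, DFM-related identification or identification by any route, and use it in the aims section, the Methods list and section 8.1. If any-route is meant, remove the DFM wording from section 8.1 and the Methods text. If DFM-related is meant, settle whether growth restriction found only at birth and perinatal death belong in the list.
2. Replace 13.52% with the per-woman rate for that definition, each woman counted once: from Femina data for DFM-related identification, or from the birth register for any route. State the source and denominator of each row.
3. Restate the effect that 538 per arm detects at that rate, and say whether it is relative or absolute.

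The cost is wording and a tabulation. The sponsor holds the Femina data, but the protocol does not show whether they, or the register, contain every component; where they do not, give a range. The stated detectable effect will probably become less favourable. The reassessment of sample size already foreseen in the Sample section is a natural place to do this.
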